### Randomization and blinding procedures

2.8

Random numbers will be generated by a computerized random number table generator using the stratified block randomization method of the SAS package (SAS statistical software version 9.4; SAS Institute Inc, Cary, NC). The random number table file will be password-protected and will be managed by an independent, blinded statistician who is not involved in participant recruitment, treatment, or assessment. Eligible subjects who provide written informed consent will be randomly assigned to a group. The participants and the researchers who evaluate the results will be unaware of which intervention group the participants have been assigned to. The wrist-ankle straps used in both groups will have the same packaging. As only one 30-minute treatment will be given, the participants will not be aware of the differences between the products during the treatment.

### Data collection and management

2.9

The CMSS and the TCM syndrome differentiation form will be used to assess the symptoms of primary dysmenorrhea in the current menstrual cycle before treatment, while the ETCS will be completed before and after the treatment. Participants will complete the general information questionnaire 3 minutes before the treatment. Researchers will ensure the reliability and validity of the questionnaire by providing guidance for each item. Clinical observation results will be recorded on a uniformly printed and numbered clinical observation form. A corresponding computer database will be established and the data will be inputted into the computer on the day of observation.

### Statistical analysis

2.10

The SPSS for Windows 21.0 will be used for statistical processing. All analyses will be conducted in accordance with the intent-to-treat principle and the per-protocol principle. Measurement data will be expressed as mean ± standard deviation, while count data will be described as number and percentage. The normal distribution test and homogeneity test of variance will be used for measurement data. The value of missing data will be defined based on the last-observation-carried-forward principle. The baseline characteristics of the 2 groups will be analyzed using the *t* test or nonparametric test. If the baseline characteristics are imbalanced, covariance analysis is used to adjust the baseline characteristics. Repeated measures analysis of variance will be adopted to analyze the outcome (analgesic effect) between groups and observed time. If necessary, a mixed model will be used to evaluate the analgesic effect. A general linear model analysis will be used to assess the correlation between patient expectations and the effect. All statistical tests will be performed on both sides, and the difference will be considered statistically significant when *P* < .05.

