##### Pain threshold measurement

2.5.2.2

The pain threshold will be measured at the Yinlingquan acupoint (SP 9) using a pressure pain detector (YISIDA, Hongkong, China). Measurements will be made 3 minutes before treatment and at the end of treatment (after the acupressure wrist-ankle strap is removed).

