### Sample size calculation

2.7

The participants will be randomly divided into the acupressure wrist-ankle strap group (intervention group) and the nonacupressure wrist-ankle strap group (control group) in a 1:1 allocation ratio. Sample size calculation is based on the primary outcome, which is proposed to be the VAS. PASS 11 software (NCSS, Kaysville, UT) was used to calculate the required sample size. Based on the preliminary experiments, the mean baseline VAS was 74 mm with a standard deviation (*σ*) of 14 mm. The researchers expect the mean difference in the VAS score between the 2 groups (*D*1) will be 10 mm and the correlation between measurement points (*ρ*) will be 0.7, which is not moderately clinically meaningful but represents a minimally important difference. With the test levels set at *α* = 0.05 (2-sided), *β* = 0.1, *D*1 = 1, *M* = 4, *σ* = 1.4, *ρ* = 0.7, and the module selected as “Tests for Two Means in a Repeated Measures Design,” where *α* represents the probability of rejecting a true null hypothesis, *β* is the probability of obtaining a false negative with the statistical test, and *M* is the number of repeated measurements. Finally, at least 32 participants are required per group. Considering a 20% dropout rate, 39 participants will be enrolled in each group, giving a total of 78 participants.

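### LOCF is the only missing-data rule for pain expected to change within 30 minutes, and the mixed model is an undefined fallback

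*Protocol article*

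**What the plan says.** Section 2.10 (Statistical analysis) of the protocol article fixes four things that bear on this point.

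- Missing values: "The value of missing data will be defined based on the last-observation-carried-forward principle". The rule is not limited to any outcome.
- Main analysis: "Repeated measures analysis of variance will be adopted to analyze the outcome (analgesic effect) between groups and observed time".
- Fallback: "If necessary, a mixed model will be used to evaluate the analgesic effect". No condition is given, and the sentence is not tied to missing data.
- Analysis sets: "All analyses will be conducted in accordance with the intent-to-treat principle and the per-protocol principle".

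Section 2.7 (Sample size calculation) allows for losses: "Considering a 20% dropout rate, 39 participants will be enrolled in each group, giving a total of 78 participants". It does not say at what stage these losses are expected.

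On timing, section 2.5.1 has the VAS read at baseline and at 5, 10 and 30 minutes. For pain threshold, section 2.5.2.2 says: "Measurements will be made 3 minutes before treatment and at the end of treatment". Section 2.5.2.4 has the ETCS completed once before and once after treatment.

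**The concern.** LOCF is unbiased only if the outcome stays level after a participant's last reading. This trial is built on the opposite expectation: the Introduction and Discussion both set out to show an immediate fall in pain over one 30-minute session. An early VAS value carried to 30 minutes therefore understates the fall in whichever arm loses the participant. For pain threshold and the ETCS, the only value available to carry is the pre-treatment one, so the participant is scored as exactly unchanged. The filled values are then analysed as if they had been observed.

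The direction of bias is not fixed. Similar losses in both arms pull the difference towards zero. Unequal losses shift one arm more than the other, and can shrink, enlarge or create a difference.

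A mixed model fitted to the observed readings does not need the fill-in, and the plan already names one. Because it is used only at discretion, with no trigger, the choice between two analyses of the primary outcome stays open until the data are seen.

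**Working it through.** **Inputs.** From section 2.7: two-sided α 0.05, β 0.1, difference 10 mm, SD 14 mm, correlation 0.7, M = 4, 32 per group before and 39 per group after the 20% allowance. From section 2.5.1: three readings after baseline. Assumptions, not in the document: when dropout occurs, how it splits between arms, the control-arm course, a 10 mm effect at every later reading, and dropout at random within arm.

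**The plan's own figure.** With equal correlation between readings:

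n = 2σ²(z₀.₉₇₅ + z₀.₉₀)²/D² × [1 + (M − 1)ρ]/M = 2 × 196 × 10.507/100 × 0.775 = 31.92, so 32 per group.

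32 × 1.2 = 38.4, so 39. The stated figures reproduce.

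**Comparator: 20% lost, observed data only.** 39 × 0.8 = 31.2, about 31 per group. For the mean of the three later readings the variance is 196 × (1 + 2 × 0.7)/3 = 156.8. The standard error is √(2 × 156.8/31) = 3.18 mm, and power is Φ(10/3.18 − 1.96) = 0.88. With the plan's M = 4 it is 0.89.

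**Upper bound under LOCF: all 20% leave both arms before the 5-minute reading.**
- Expected difference: 0.8 × 10 = 8 mm.
- Variance in an arm with mean fall δ: 0.8 × 156.8 + 0.2 × 196 + 0.2 × 0.8 × δ² = 164.64 + 0.16δ².
- Control arm flat (δ = 0 and 10): variances 164.64 and 180.64; standard error √(345.28/39) = 2.98; power Φ(8/2.98 − 1.96) = 0.77.
- Control falls of 5, 10 and 20 mm (mean 11.67, so δ = 11.67 and 21.67): variances 186.4 and 239.8; standard error √(426.2/39) = 3.31; power Φ(8/3.31 − 1.96) = 0.68.

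**Dropout spread evenly over the three later readings.** With a constant 10 mm effect, only those lost before 5 minutes carry a baseline value: 20%/3 = 6.7%. The difference is 10 × (1 − 0.067) = 9.3 mm.

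**Unequal dropout before 5 minutes, 30-minute falls of 30 mm (intervention) and 20 mm (control).**
- 10% intervention, 30% control: 0.9 × 30 − 0.7 × 20 = 27 − 14 = 13 mm.
- 30% intervention, 10% control: 0.7 × 30 − 0.9 × 20 = 21 − 18 = 3 mm.

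**Simulation** (39 per arm, 2,500 runs per scenario, *t* test, true difference 10 mm). Each cell gives the estimated difference and power. The last column uses participants with all three later readings.

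| Dropout, intervention/control; control course | LOCF, mean of 3 readings | LOCF, 30 min | Observed, mean of 3 readings |
|---|---|---|---|
| 20/20 before 5 min; flat | 8.0 mm, 0.76 | 8.1 mm, 0.69 | 10.0 mm, 0.87 |
| 20/20 before 5 min; falling | 8.1 mm, 0.69 | 8.2 mm, 0.54 | 10.1 mm, 0.89 |
| 20/20 spread; flat | 9.3 mm, 0.88 | 9.3 mm, 0.81 | 10.0 mm, 0.87 |
| 20/20 spread; falling | 9.3 mm, 0.84 | 9.3 mm, 0.73 | 10.0 mm, 0.87 |
| 10/30 before 5 min; falling | 11.3 mm, 0.94 | 13.0 mm, 0.92 | 10.0 mm, 0.86 |
| 30/10 before 5 min; falling | 4.7 mm, 0.29 | 3.0 mm, 0.12 | 10.1 mm, 0.87 |

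A repeat of the second row gave a power of 0.66, so the upper-bound range is 0.66 to 0.76. Observed data at 30 minutes alone gave power of about 0.78 to 0.80 throughout.

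**Type I error under LOCF, no true effect, control falling.** With equal dropout it stays near 0.05. With a 10%/30% split either way before 5 minutes it is about 0.11 for the mean and 0.19 to 0.20 at 30 minutes. With the same split spread over time it is 0.07 to 0.08 and 0.13 to 0.14.

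The *t* test stands in for the planned repeated measures analysis, so these figures show direction and order of size, not the exact power of the planned test.

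**The case against.** The strongest reply is that little data may be missing where LOCF can act. Treatment is one supervised 30-minute session, and section 2.7 gives only a 20% allowance with no timing. Many losses may come before the session, for instance through non-attendance or analgesic use that triggers the exclusion in section 2.3.2. Those participants have no baseline VAS, so LOCF has nothing to carry, and a baseline-adjusted mixed model would not recover them either. This stands. A reader might infer that all of the planned 20% will enter as no-change values, but the document does not support that. Even within the session, a carried value means no change from baseline only for someone who leaves before 5 minutes.

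A reader might also compute a fall in power from 94% to 81%, using the three later readings at 39 per group with 10 mm and then 8 mm. That comparison fails on both sides. The 94% assumes no dropout at all, and the 81% keeps the complete-data SD and so omits the extra variance from mixing dropouts with completers.

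Nor does adding 20% to the sample contradict LOCF. An allowance for non-evaluable participants is compatible with the intent-to-treat and per-protocol analyses both planned. The per-protocol analysis does not repair the intent-to-treat result, however.

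The unequal-dropout splits and falls are illustrations. The idea that control women would leave because pain persists has little support: participants are to be blinded (section 2.8), and follow-up treatment is offered after the 30 minutes (section 2.3.4).

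Finally, the covariance structure and a missing-not-at-random sensitivity analysis may properly sit in an analysis plan that is not shown. Their absence is no fault here. The LOCF rule and the open-ended fallback are different, because the article states both.

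**Conclusion.** The point holds as a criticism of a stated rule, with a size that cannot be fixed from the document. LOCF conflicts with the trial's own expectation of change within the session, and it can bias the intent-to-treat result in either direction. At the planned rate with equal arms, the effect on a 10 mm difference runs from small (about 9.3 mm, little loss of power on the averaged readings) to material (8 mm, power about 0.7 against about 0.88). If few participants are lost after the baseline VAS, it is smaller still. With unequal losses and a falling control arm, LOCF does not reliably protect the 5% error rate. All of this rests on the assumed timing, split and control course, and on dropout that is random within arm. The point should be corrected, but it does not invalidate the trial.

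**What to change.** In section 2.10, delete the LOCF sentence for the primary analysis. Make a linear mixed model the primary analysis, fitted to all observed VAS values at 5, 10 and 30 minutes, with group, time, group × time and baseline VAS. Remove the conditional wording so that the model is fixed in advance. State that the model is fitted to observed values, since fitting it to LOCF-filled data would keep the problem. LOCF may stay only as a labelled sensitivity analysis.

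The cost is wording and a little analysis work in the SPSS software already named, with no extra participants or measurements. The price in assumptions is reliance on data missing at random: if dropout depends on pain that was never recorded, the mixed model can be biased too.

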#### Primary outcome measures

2.5.1

The primary outcome measure is the abdominal pain intensity score assessed by VAS. Abdominal pain will be quantified using the VAS score as determined on a 100-mm horizontal line (0, no pain; 100, pain intolerable). On the VAS scale, the score is based on the horizontal distance from the leftmost pain free to the edge marked by the patient. The distance represents pain intensity. The VAS will be assessed at baseline (3 minutes before intervention) and at 5, 10, and 30 minutes (after the removal of the wrist-ankle strap).

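### Baseline VAS is adjusted for only if a baseline test shows imbalance; adjusting in every case is more precise and costs almost nothing

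*Protocol article*

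**What the plan says.** The relevant text is in three sections of the protocol article.

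- **Statistical analysis (2.10).** Baseline is first tested: "The baseline characteristics of the 2 groups will be analyzed using the *t* test or nonparametric test". Adjustment then depends on what is found: "If the baseline characteristics are imbalanced, covariance analysis is used to adjust the baseline characteristics". No threshold for imbalance is given, and baseline VAS is not named as a covariate. The main analysis is: "Repeated measures analysis of variance will be adopted to analyze the outcome (analgesic effect) between groups and observed time". A mixed model is held in reserve. The section does not say whether the group main effect or the group-by-time term decides the result.
- **Primary outcome measures (2.5.1).** "The VAS will be assessed at baseline (3 minutes before intervention) and at 5, 10, and 30 minutes". That is one reading before treatment and three after.
- **Sample size calculation (2.7).** SD 14 mm, difference 10 mm, correlation 0.7 between measurement points, M = 4 repeated measurements, two-sided 5%, 90% power. This gives 32 per group, raised to 39 for dropout. M = 4 matches baseline plus the three later readings, so baseline VAS appears to be one of the repeated measures.

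**The concern.** Under randomisation every baseline difference is a chance difference. A test of it therefore says nothing about whether a covariate is worth including. The useful question is how strongly the covariate predicts outcome, and for baseline VAS the protocol has already given its answer: 0.7. The rule brings in this covariate only when a test happens to flag a difference, so the data choose the model for the primary outcome.

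Two things are at stake. One is precision that the trial has already paid for by collecting baseline VAS in everyone. The other is how a realised imbalance too small to be flagged feeds into the estimate. The size of both depends on which term of the repeated measures analysis decides, and the section leaves that open.

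**Working it through.** **Inputs** (Sample size calculation): σ = 14 mm, D = 10 mm, ρ = 0.7, M = 4, α = 0.05 two-sided, power 90%, n = 32 evaluable and 39 enrolled per group. **Assumptions added here:** compound symmetry; the same SD at all times; ρ = 0.7 also between baseline and later readings; baseline VAS is among the characteristics tested; imbalance is flagged at 5%.

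**1. The plan's own figure.** The variance of the mean of four readings is σ²(1 + 3ρ)/4 = 196 × 0.775 = 151.9 mm², so the SD is 12.32 mm. Then n = 2 × (1.960 + 1.282)² × 151.9 / 10² = 31.9, rounded up to 32. The stated figure reproduces. It powers a 10 mm difference in the mean of all four readings.

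**2. Variance of the between-group quantity under three analyses of the post-baseline mean.**
- Unadjusted post-baseline mean: (1 + 2ρ)/3 = 0.80, so 156.8 mm².
- Change from baseline (a group-by-time contrast): 0.80 + 1 − 2ρ = 0.40, so 78.4 mm².
- Post-baseline mean adjusted for baseline: 0.80 − ρ² = 0.31, so 60.8 mm².

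Always adjusting cuts variance by 1 − 0.31/0.80 = 61% against the first and by 1 − 0.31/0.40 = 22.5% against the second.

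**3. Difference detectable with 90% power at 39 per group**, 3.242 × √(2 × variance/39):
- Unadjusted: 9.2 mm.
- Change: 6.5 mm.
- Adjusted: 5.7 mm.

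At 32 per group, power for 10 mm is 89%, 99.5% and 99.9% respectively. The omnibus group-by-time test has 97.6%.

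**4. Group main effect over all four readings.** Randomisation implies no expected baseline difference, so a 10 mm effect after treatment averages to (0 + 10 + 10 + 10)/4 = 7.5 mm. The SE at 32 per group is 12.32 × √(2/32) = 3.08 mm, and 7.5/3.08 = 2.43. Power is about 68%; 57 per group would be needed for 90%.

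**5. Imbalance that goes unflagged.** The SE of the baseline difference is 14 × √(2/n): 3.17 mm at 39 per group and 3.5 mm at 32. The t test flags differences above 1.99 × 3.17 = 6.3 mm, or 2.00 × 3.5 = 7.0 mm. At the 7.0 mm limit the error, given that imbalance, is:
- Post-baseline mean: 0.7 × 7.0 = 4.9 mm.
- Four-reading mean: 0.775 × 7.0 = 5.4 mm.
- Change from baseline: (1 − 0.7) × 7.0 = 2.1 mm in the opposite direction, that is, over-corrected.

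These are limits. At 39 per group the median absolute imbalance is 0.674 × 3.17 = 2.1 mm, which carries 0.7 × 2.1 = 1.5 mm into the post-baseline comparison.

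**6. Behaviour of test-then-adjust over all randomisations** (simulation, 40,000 trials, 32 per group).
- Mean estimate: within about 0.01 mm of 0 under no effect, and of −10 under a 10 mm effect.
- Type I error: 3.3% when the fallback is the unadjusted post-baseline mean, 4.6% when it is change from baseline.
- Power for the first version: 90.3%, against 99.9% for adjusting always.

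**7. Sensitivity to ρ.** The variance cut against the unadjusted mean and against change is 37.5% and 37.5% at ρ = 0.5, and 74% and 15% at ρ = 0.8. Adjustment is more precise throughout.

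**The case against.** The strongest reply is that the documents never state an unadjusted comparison of post-baseline scores. Four time points and M = 4 suggest that baseline is already in the repeated measures analysis. If group-by-time decides, most of the information in baseline is used and power is ample without a covariate. This stands. A reader might infer that the plan throws away most of the precision in baseline VAS; that is true only of the post-only reading, which no section specifies. The 61% and the fall from 9.2 to 5.7 mm carry that condition.

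A reader might also infer that the rule biases the result or invalidates the P value. It does neither. The error in step 5 is conditional on the imbalance that occurred. Over all randomisations the estimate is unbiased, and the two-stage rule is slightly conservative. Large unflagged differences are also uncommon: at 39 per group, one between 6.0 and 6.3 mm arises in about 1% of randomisations.

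Finally, one might fault the analysis for omitting the randomisation strata. Randomization and blinding procedures (2.8) says only that numbers are generated "using the stratified block randomization method of the SAS package" and names no factor. A condensed article may leave this to the full protocol or analysis plan, so the omission cannot be held against it.

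What the reply does not rescue is the rule itself. It is stated, not merely left out; it rests on a test that cannot answer the question; and unconditional adjustment does better on every reading examined.

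**Conclusion.** The point holds as a matter of efficiency and prespecification, not validity. Making adjustment depend on a baseline test gives up precision. The size depends on the unnamed deciding term: 61% of variance if post-baseline scores are compared unadjusted, about 22.5% if change from baseline is. If the four-reading group effect decides, the main harm is dilution to 7.5 mm and power of about 68% at 32 per group. Chance imbalance below 6.3 mm (39 per group) or 7.0 mm (32) is left uncorrected, or over-corrected by a change contrast.

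The figures rest on compound symmetry, a constant SD of 14 mm, ρ = 0.7 throughout and a 5% flagging level. The direction of the precision gain does not depend on the exact value of ρ within the range examined. This is an improvement available at essentially no cost.

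**What to change.** In Statistical analysis (2.10):

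- Remove the baseline test as the trigger for adjustment. Baseline characteristics can still be described by group.
- Fix the primary model in advance: VAS at 5, 10 and 30 minutes as outcomes; baseline VAS as covariate in every case, and no longer among the outcomes; group, time and group-by-time as terms.
- Name the contrast that decides the result, for example the adjusted group difference averaged over the three readings or at one stated time.
- Include the randomisation strata if the full protocol defines any.

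The cost is a change of wording and one or a few degrees of freedom. Baseline VAS is already collected and no further participants are needed. The change should be made before unblinding, because it selects the model for the primary outcome.

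### Allocation is stratified but the primary VAS model names no strata; the test of the group effect is conservative to the extent that the strata predict VAS

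*Protocol article*

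**What the plan says.** Section 2.8 (Randomization and blinding procedures) generates the allocation "using the stratified block randomization method of the SAS package". It names neither the stratification factors nor the block size.

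Section 2.10 (Statistical analysis) gives the main analysis: "Repeated measures analysis of variance will be adopted to analyze the outcome (analgesic effect) between groups and observed time". Group and time are the only terms named. Covariates come in by a conditional rule. First, "The baseline characteristics of the 2 groups will be analyzed using the *t* test or nonparametric test". Then, "If the baseline characteristics are imbalanced, covariance analysis is used to adjust the baseline characteristics". There is also a fallback, "If necessary, a mixed model will be used to evaluate the analgesic effect", with no covariates listed. Nowhere does the article say that the stratification factors enter a model.

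Section 2.7 (Sample size calculation) sizes the trial on the difference in mean VAS between the two groups in a repeated measures design and concludes that "at least 32 participants are required per group".

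**The concern.** Stratified blocks make the arms nearly equal on the stratification factors. This takes between-stratum variation out of the true sampling variance of the group difference. An ANOVA without strata leaves that variation in its error term, so its standard error describes a less precise trial than the one that was run.

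The covariate rule in section 2.10 does not repair this. It looks for baseline differences between the arms, and stratification is designed to prevent such differences on exactly these factors. Followed as written, the rule will therefore tend to leave out the variables on which the trial randomised.

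At stake are the width of the confidence interval and some power for the group effect, in a trial with about 32 evaluable women per group. The risk of a false positive is not raised.

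**Working it through.** **Inputs from section 2.7:** σ = 14 mm, ρ = 0.7, M = 4 readings, difference 10 mm, two-sided α = 0.05, power 90%, 32 evaluable per group. Section 2.5.1 gives the four readings: baseline, 5, 10 and 30 minutes.

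**Assumed input:** R2, the share of the variance of a woman's mean VAS that the strata explain. The article gives no value, so a range is shown.

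**Step 1: reproduce the plan's figure.** Under compound symmetry the variance of a woman's mean is σ²(1 + 3ρ)/4 = 196 × 3.1/4 = 151.9 mm², an SD of 12.32 mm. Then n = 2 × 151.9 × (1.960 + 1.282)²/10² = 31.92, so 32 per group, with power 90.1%. The stated figure reproduces. It is a figure for the between-subject group effect.

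**Step 2: effect of leaving the strata out.** The SE used by the unadjusted test is √(2 × 151.9/32) = 3.08 mm. With balanced strata the true SE is 3.08 × √(1 − R2), so the planned SE is too large by the factor 1/√(1 − R2). Hence, for a true difference δ:

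- actual alpha = 2 × [1 − Φ(1.96/√(1 − R2))]
- unadjusted power = Φ[(δ/3.08 − 1.96)/√(1 − R2)]
- adjusted power = Φ[δ/(3.08 × √(1 − R2)) − 1.96]

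With δ = 10 mm at all four readings:

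| R2 (assumed) | SE too large by | Actual alpha | Power, unadjusted | Power, adjusted | Gain (points) |
|---|---|---|---|---|---|
| 0 | 0% | 5.0% | 90.1% | 90.1% | 0 |
| 0.1 | 5.4% | 3.9% | 91.2% | 92.8% | 1.6 |
| 0.2 | 11.8% | 2.8% | 92.5% | 95.2% | 2.7 |
| 0.3 | 19.5% | 1.9% | 93.8% | 97.3% | 3.5 |

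**Step 3: simulation.** The setting was 64 women, two equal strata, permuted blocks of 4, 10,000 null runs, and 4,000 runs at 10 mm.

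| R2 | Alpha, group, unadjusted | Alpha, group, adjusted | Alpha, group-by-time | Power, unadjusted | Power, adjusted |
|---|---|---|---|---|---|
| 0 | 5.2% | 5.3% | 5.0% | 89.2% | 89.2% |
| 0.1 | 3.7% | 4.9% | 4.8% | 90.5% | 92.2% |
| 0.3 | 1.8% | 4.6% | 4.6% | 91.8% | 96.4% |

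The simulation uses t tests, so its powers lie somewhat below the normal formulas (89.2% against 90.1% at R2 = 0). Its gains are slightly larger, but with 4,000 runs each power has a Monte Carlo error of about 0.4 to 0.5 points. The alphas agree with Step 2. In these runs the stratum effect was constant over time, so it cancels from the group-by-time test, which keeps its level without adjustment.

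**The case against.** The strongest objection is that the size of the effect has no anchor in the article. No stratum is named. The trial has one university, one acupuncturist and women aged 18 to 30, so site, operator and sex cannot be strata and age can vary little. The strata may predict VAS hardly at all. This stands: the conclusion has to be conditional, and an unconditional statement that the P values are too conservative is not supported.

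Second, section 2.10 does not say which ANOVA term decides efficacy. With baseline among the four readings, group-by-time is a natural candidate, and it is not affected by a stratum effect that is constant over time. Nor is it short of power on the plan's inputs. The variance of the mean of the three later readings minus baseline is 196 × (0.8 + 1 − 1.4) = 78.4, so the SE is √(2 × 78.4/32) = 2.21 mm. A 10 mm effect after treatment then gives Φ(10/2.21 − 1.96), about 99%. This also stands, and it confines the point to the group main effect. That effect still matters because it is the one on which section 2.7 sizes the trial.

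Third, a reader might infer a much larger loss. If 10 mm applies only to the three readings after baseline, the average over four is 7.5 mm, and power runs from 69.1% unadjusted to 72.8% adjusted at R2 = 0.1, and from 71.5% to 82.9% at R2 = 0.3. But power at 7.5 mm is already Φ(7.5/3.08 − 1.96) = 68% at R2 = 0, where strata play no part. Most of the shortfall comes from averaging in the pre-treatment reading, which is a separate matter.

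Fourth, the article is condensed, and a full protocol or SAP may name the strata and put them in the model. Silence on the names is therefore no fault. What remains is that the article does state a rule for admitting covariates, and that rule is poorly suited to factors that the design has balanced.

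**Conclusion.** The point holds in a limited, conditional form. As written, the analysis does not use the strata by which the trial randomises, and the imbalance rule will rarely bring them in. If the strata explain 10% to 30% of the variance in mean VAS, the test of the group effect runs at about 3.9% down to 1.9% instead of 5%, and adjustment would add about 1.6 to 3.5 points of power at 10 mm. If they explain nothing, nothing is lost.

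A reader might infer that the trial is invalid or underpowered for this reason. The documents do not support that. Type I error is not inflated. On the normal approximation that reproduces the plan's own figure, unadjusted power at 10 mm over all readings stays at or above 90%.

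The figures assume 32 evaluable women per group, compound symmetry, balanced strata and stratum effects constant over time. This is a minor improvement in precision.

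**What to change.** In section 2.10, state that the primary VAS model will contain treatment, time, treatment-by-time and the randomisation stratification factors as fixed effects, whatever the baseline tests show. Use the same stratification terms in the pain threshold and skin temperature models, and in the mixed model if it is used. Name the factors so that the sentence can be applied. The imbalance rule should not govern whether these factors are included.

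The cost is one sentence and the degrees of freedom for the strata; their number is not given in the article. No participants or visits are added, and the stratum of each woman has to be known to allocate her.

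### Section 2.10 does not say which repeated measures ANOVA effect decides the trial, and with baseline among the four readings the group effect has about 68% power, not 90%

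*Protocol article*

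**What the plan says.** - **Primary outcome (section 2.5.1):** "The VAS will be assessed at baseline (3 minutes before intervention) and at 5, 10, and 30 minutes", the last reading being taken after the strap is removed. No time point, summary over time or change measure is singled out.
- **Analysis (section 2.10):** "Repeated measures analysis of variance will be adopted to analyze the outcome (analgesic effect) between groups and observed time". A mixed model may be used if needed. Covariance adjustment is planned only when baseline characteristics turn out to be imbalanced. One two-sided threshold, P < .05, applies to all tests.
- **Sample size (section 2.7):** "The researchers expect the mean difference in the VAS score between the 2 groups (*D*1) will be 10 mm", "the mean baseline VAS was 74 mm with a standard deviation (*σ*) of 14 mm" and "the correlation between measurement points (*ρ*) will be 0.7". The inputs are then entered on a 0 to 10 scale: "With the test levels set at *α* = 0.05 (2-sided), *β* = 0.1, *D*1 = 1, *M* = 4, *σ* = 1.4, *ρ* = 0.7". The PASS module compares two means in a repeated measures design. The result is 32 per group, raised to 39 for dropout.

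**The concern.** A repeated measures ANOVA of two groups over several times gives two tests that speak to treatment. The group effect asks whether the arms differ on average over all readings. The group-by-time interaction asks whether the arms follow different courses. Section 2.7 points to the first of these, but section 2.10 does not carry that choice over. If the decision is left until the data are in, either result can be presented as proof of benefit, and the 5% level is not protected.

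The two tests also behave very differently when the strap works. A reading taken before treatment cannot show a treatment effect. Including it in the average pulls the group effect towards zero. The interaction does pick up the change from baseline, but it is a test on several degrees of freedom with no single estimate in mm to set against the 10 mm target. The trial could therefore miss a real 10 mm benefit on the test that matches its sample size, or succeed on a test that does not estimate the benefit.

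**Working it through.** **Inputs.** From section 2.7: target difference 10 mm, SD σ = 14 mm, correlation ρ = 0.7, M = 4 measurements, two-sided α = 0.05, power 90%, n = 32 per group. From section 2.5.1: VAS at baseline, 5, 10 and 30 minutes. Two assumptions are added: equal correlation between all pairs of readings, and a 10 mm effect at each of the three post-baseline readings.

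**1. Reproducing the plan's figure.**
- The SD of a participant's mean over M readings is σ√[(1+(M−1)ρ)/M]. With M = 4 it is 14 × √(3.1/4) = 14 × √0.775 = 12.32 mm.
- n per group = 2 × [12.32 × (1.960 + 1.282)/10]² = 31.92, so 32. Power at 32 is 90.1%.
- The stated 32 therefore reproduces as an unadjusted comparison of means over four readings, with the full 10 mm present in that four-reading average.

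**2. The group effect when one of the four readings is baseline.**
- Randomised arms have an expected baseline difference of 0. The four-reading average is then (0 + 10 + 10 + 10)/4 = 7.5 mm.
- SE at 32 per arm = 12.32 × √(2/32) = 3.08 mm.
- 7.5/3.08 = 2.43. Power = Φ(2.43 − 1.96) = Φ(0.47), about 68%. Simulation of the ANOVA gives about 67%.
- To keep a 10 mm four-reading average, the post-treatment effect would have to be 10/0.75 = 13.3 mm.

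**3. The interaction under the same 10 mm effect.** Simulated power at 32 per arm is about 97% to 98%. The group test and the interaction give different verdicts in about 34% of such trials, so the choice between them matters in practice.

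**4. False-positive rate if either test may count.**
- If the tests are independent: 1 − 0.95² = 9.75%.
- Simulated at ρ = 0.7 (20,000 null trials, interaction with Greenhouse-Geisser correction): 9.4% at 32 per arm and 9.5% at 39.
- Over ρ from 0.5 to 0.9 the rate stays between 9.3% and 9.9%.
- With one test named in advance, the group effect alone gives 4.9%.

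**5. The alternative: mean of 5, 10 and 30 minutes, adjusted for baseline.**
- Variance of the three-reading mean: σ²(1 + 2ρ)/3 = 0.80σ².
- Its covariance with baseline is ρσ², so adjustment removes ρ²σ² = 0.49σ². This leaves 0.31σ².
- SD = 14 × √0.31 = 7.79 mm. SE at 32 per arm = 7.79 × √(2/32) = 1.95 mm.
- 10/1.95 = 5.13. Power = Φ(5.13 − 1.96) = Φ(3.17), about 99.9%.

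**6. Sensitivity to ρ (32 per arm, σ = 14 mm, same formulas).**

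| ρ | Group effect with baseline included (7.5 mm) | Baseline-adjusted mean of three (10 mm) |
|---|---|---|
| 0.5 | 77% | 99.3% |
| 0.7 | 68% | 99.9% |
| 0.9 | 61% | above 99.9% |

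The ranking does not depend on the exact correlation.

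**The case against.** **The article does point to a primary comparison.** Section 2.7 sizes the trial on one mean difference between groups ("The researchers expect the mean difference in the VAS score between the 2 groups"), which corresponds to the group effect. This stands, and it would be too flat to say that the document has no primary comparison in mind. But section 2.10 never commits to it, and with baseline among the readings it is the weaker of the two tests.

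**No success rule is stated, and a SAP may settle it.** The single P < .05 threshold is a rule for each test, not a definition of trial success. The 9.5% is therefore conditional: it applies if either effect may be claimed. A SAP that is not shown could name one. That would restore the 5% level, but it would not cure the dilution if the term it named were a group effect with baseline included.

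**Baseline in the ANOVA is an inference.** Section 2.10 does not list the readings that enter the model. The inference rests on M = 4 in section 2.7 and exactly four readings in section 2.5.1. If baseline were left out, there would be three repeated measurements and M = 4 would not match the schedule. The dilution would then vanish: the unadjusted three-reading mean needs 33 per group, almost what was planned.

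**A stronger reading that the text does not support.** A reader might infer separate group comparisons at 5, 10 and 30 minutes, each at P < .05, and an overall error near 15% if any of five tests could count. Section 2.10 plans no such comparisons. The Discussion's remark about focusing on three time points is made while explaining the single-session limitation and is not an analysis rule. The 15% figure should not be attached to this plan.

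**Conclusion.** The concern holds in two linked parts.

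- **Undecided test.** Section 2.10 leaves open whether the group effect or the interaction decides. If either may, the false-positive rate is about 9.5% instead of 5%.
- **Diluted effect.** If baseline is one of the four repeated measures, as M = 4 suggests, the group effect carries 7.5 mm of a 10 mm benefit. Power at 32 per arm is about 68% against the planned 90%.

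The power figures rest on SD 14 mm, ρ = 0.7 between all pairs of readings, and a full 10 mm effect at 5, 10 and 30 minutes. A slower onset would lower the three-reading average and the power of any test built on it. The power loss is a separate matter from the error rate, and neither should be cited as evidence for the other. This is more than a request for detail, because readings already planned support a clearly better primary test.

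**What to change.** - **Sections 2.5.1 and 2.10:** name one primary test, the group difference in VAS averaged over 5, 10 and 30 minutes. Adjust it for baseline VAS in every case, not only after an imbalance is found. Report it with a 95% CI in mm, at two-sided .05.
- **Section 2.10:** make the group-by-time test and any comparisons at single times secondary, with no claim of efficacy resting on them alone.
- **Section 2.7:** state that this contrast differs from the unadjusted mean of four readings on which the 32 per group was calculated. Restate the power for it: about 99.9% at 32 per arm under SD 14 mm and ρ = 0.7.

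The cost is one sentence in each of the three sections. No added participants, visits or measurements are needed. The change should be dated and made before allocation is unblinded.
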